### Participants and Recruitment

The inclusion, exclusion, and exit criteria are listed in Textbox 1.

Textbox 1.Inclusion, exclusion, and exit criteria.
**Inclusion criteria**
Individuals who satisfy the subsequent criteria will be incorporated into the trial:Diagnosis of mild to moderate CHE by the diagnostic criteria established in the Chinese Expert Consensus on the Diagnosis and Treatment of Hand Eczema (2021 Edition) [26] (HECSI score ≤27).Diagnosis of chronic eczema classified as blood deficiency and wind-dry type according to the Expert Consensus on the Diagnosis and Treatment of Eczema in Traditional Chinese Medicine (2021 Edition) [27].Patients aged 18-70 years (inclusive), both male and female.The primary affected region is the hands.Signed clinical informed consent and ability to adhere to the treatment protocol.
**Exclusion criteria**
Individuals meeting any of the following criteria will be excluded from participationPresence of any systemic or active skin disorders (eg, psoriasis) or conditions that could affect the evaluation of skin lesions, such as scars, tattoos, birthmarks, or other pigmentary skin conditions.Existence of specific bacterial, viral, or fungal infections at the site of application that require antibiotic therapy.The presence of serious concomitant primary diseases impacting the heart, cerebrovascular system, liver, kidneys, or hematological system, along with individuals experiencing mental health issues.Use of systemic corticosteroids or immunosuppressants within the 30 days leading up to treatment; administration of biologics or small molecule medications within the preceding 90 days; or application of topical corticosteroids or retinoids within a week prior to treatment.Confirmed allergies to any component of the investigational drug.Pregnant or breastfeeding individuals, as well as those planning to conceive in the next 3 months.Participation in other clinical trials for pharmaceuticals in the last 3 months.
**Exit criteria**
Patients will be withdrawn from the trial under the following conditions:Protocol noncompliance: Missing one or more scheduled follow-up visits without prior notification or valid justification; failure to complete at least 80% of the required clinical assessments (eg, symptom diaries and laboratory tests).Safety or medical reasons: Development of a new condition (eg, severe infection and pregnancy) requiring intervention that conflicts with the trial; concurrent use of medications outside the prescribed protocol, particularly those affecting the evaluation of the investigational drug’s efficacy or safety.Participant-initiated withdrawal: Voluntary withdrawal via written or verbal request; loss to follow-up (no contact for 14 days or more despite 3 attempted reach-outs via phone or email).Other: Death or investigator-determined necessity to terminate the trial (eg, Grade 3 or higher adverse event).

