### Data Analyses

The results of this trial will be analyzed from three perspectives:

Full Analysis Set (Intention-to-Treat Analysis): This set includes all randomized participants, with data analyzed according to the principle of “randomization equals analysis.” Missing data will be addressed using multiple imputation methods. Predictive mean matching will be used for continuous variables while logistic regression imputation will be used for categorical variables.Per Protocol Set: This set comprises participants who meet specific criteria; that is, they must have completed at least 80% of the treatment regimen (ie, a minimum of 22 days of medication within 4 weeks), have not used prohibited study drugs, and possess complete data for the primary end point (HECSI score).Safety Set: This set includes all participants who received at least 1 dose of the study medication.

The variable processing and statistical methods for this trial are outlined as follows: (1) continuous variable data that adhere to a normal distribution will be presented as mean (SD). Independent sample *t* tests (2-tailed approach) will facilitate between-group comparisons while repeated measures ANOVA will be applied for comparisons across multiple time points (eg, baseline, during treatment, and post treatment); (2) data that do not conform to a normal distribution will be expressed as median (IQR), with between-group comparisons executed using the Mann-Whitney *U* test; (3) categorical data will be described in terms of proportions or percentages, with between-group comparisons conducted using chi-square tests or Fisher exact test, depending on the final sample size. (4) All data processing and chart generation will be performed using R 4.0 software (R Project for Statistical Computing). Statistical tests will be 2-sided, with a significance level at *P*<.05.

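### The exit criteria end outcome collection after a protocol deviation, so week-4 values that could be observed must be imputed in the all-randomised analysis

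*Protocol article*

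**What the plan says.** In the Protocol article, the exit criteria in Textbox 1 open with "Patients will be withdrawn from the trial under the following conditions". What ends is therefore participation in the trial, not merely use of study drug. Three of the listed triggers are events after randomisation that do not in themselves prevent a later assessment:

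- "Missing one or more scheduled follow-up visits without prior notification or valid justification";
- "failure to complete at least 80% of the required clinical assessments";
- "concurrent use of medications outside the prescribed protocol, particularly those affecting the evaluation of the investigational drug", which is listed among the safety or medical reasons.

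The abstract gives assessments at baseline, 2 weeks and 4 weeks, and Primary Outcomes names HECSI and NRS.

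For the full analysis set, Data Analyses says "This set includes all randomized participants". It adds "Missing data will be addressed using multiple imputation methods", by predictive mean matching for continuous variables and logistic regression for categorical ones. The per-protocol set already leaves out patients who took prohibited drugs, those under 80% of treatment, and those without complete HECSI data.

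The article describes no outcome collection after exit. Quality Control only has the reason for withdrawal recorded. The one sensitivity analysis named (under Intervention) concerns drug adherence below 80% or above 120%.

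**The concern.** An all-randomised analysis is only as good as the outcomes collected from all randomised patients. Here the rule on who leaves works against the rule on who is analysed. A patient who skips week 2 without notice, or who uses another medication, is taken out before the week-4 assessment even if willing to attend it. The gap is then filled by a model.

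That matters because the reasons for exit are not obviously unrelated to outcome. Turning to another treatment can signal poor response, and a missed visit may do so too. Sample Size calls this a noninferiority trial with a margin of 0.095, so a shift of a few points in the difference between arms can decide the conclusion. The per-protocol set is no independent check, because it requires complete HECSI data and so drops the same patients.

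**Working it through.** **The plan's own figures.** Sample Size gives control rate 0.53, RZZYL rate 0.7347, margin 0.095, and z-values 1.95996 and 1.28155.

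- n per arm = (1.95996 + 1.28155)² × [0.53×0.47 + 0.7347×0.2653] / (0.53 − 0.7347 − 0.095)² = 51.94, so 52 against the stated 53.
- 53 × 1.15 = 60.95, which gives the stated 61 per arm.

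The figures are reproduced to within one patient. At the planned 15% attrition, 0.15 × 61 = 9.15, so about 9 patients per arm could need an imputed week-4 outcome. The article does not say how many of these would arise from the exit rules.

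**Which triggers cost a week-4 value.**

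| Trigger | Effect on the week-4 outcome |
|---|---|
| Unexcused week-2 absence | Patient is out before week 4; the value is lost by rule |
| Outside medication before week 4 | Patient is out before week 4; the value is lost by rule |
| Unexcused week-4 absence | The value is missing with or without the rule |
| Under 80% of assessments | Usually judged near the end, so few values are lost |

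The first two rows carry the point.

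**How far the comparison could move.** The illustration uses response rates because the margin is stated on that scale. Assumptions, none of them from the documents: the true RZZYL rate is 43.5%, against the documents' 53% for mometasone, so the true difference is −9.5 points; only non-responders exit, a fraction f of them; and each leaver is imputed at the rate seen among those who stay in the same arm. Then

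apparent rate = p / [p + (1 − p)(1 − f)].

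- RZZYL, f = 0.25: 0.435 / (0.435 + 0.565×0.75) = 0.507
- RZZYL, f = 0.10: 0.435 / (0.435 + 0.565×0.90) = 0.461
- Mometasone, f = 0.10: 0.53 / (0.53 + 0.47×0.90) = 0.556
- Mometasone, f = 0.25: 0.53 / (0.53 + 0.47×0.75) = 0.601

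| Non-responders who exit (RZZYL / mometasone) | Apparent difference, from unrounded rates | True difference |
|---|---|---|
| 25% / 10% | −0.050 | −0.095 |
| 10% / 10% | −0.095 | −0.095 |
| 25% / 25% | −0.094 | −0.095 |
| 10% / 25% | −0.140 | −0.095 |

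In the first row the exits are 0.565×0.25 = 14% of the RZZYL arm and 0.47×0.10 = 5% of the mometasone arm. Unequal exit moves the difference by about 4.5 points either way, while equal exit hardly moves it.

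**What the illustration leaves out.** The formula imputes at the raw completer rate. An imputation model that uses baseline and week-2 scores would soften these shifts for patients who leave after week 2. A patient removed for missing week 2 has no week-2 value to use.

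**The case against.** The strongest reply is that the plan already includes everyone. The full analysis set contains all randomised patients, and multiple imputation assumes only that leavers resemble stayers given the observed data, not unconditionally. Both statements are correct. A reader might infer that the exit rules defeat the intention-to-treat set, or that imputation simply turns failures into completers; the documents support neither. What is lost is the outcome, not the patient's place in the set.

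It is also tempting to say that the rules favour a false claim of noninferiority. The table does not bear that out: with equal exit there is almost no shift, and with more exit on mometasone the deficit is exaggerated. Nothing in the article indicates which arm would lose more patients, and that leavers are failures is itself an assumption, less certain for a missed visit than for outside medication.

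The missed-visit rule is also narrower than it may look. It applies only without notice or justification, and Recruitment provides reminders, weekend slots and a completion subsidy. Concomitant Treatments has medication documented up to the final follow-up visit.

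Finally, outside medication sits under safety or medical reasons, so it could be said that the rule should be left alone. That holds for treatment decisions, which this point does not touch. It does not explain why measurement must stop.

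What remains after all this is that the exit rule is stated, no section restores the lost outcomes, and the named sensitivity analysis concerns adherence rather than the missing-data assumption.

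**Conclusion.** The point stands as an avoidable loss of data. Followed as written, Textbox 1 discards week-4 HECSI and NRS values that could be obtained, and the all-randomised analysis then depends on a missing-at-random assumption that those values would have made largely unnecessary.

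The possible bias has no fixed sign. Under the stated assumptions a true 9.5-point deficit could appear as anything from about 5.0 to about 14.0 points, and as 9.4 to 9.5 when exits are equal. These figures illustrate sensitivity and do not predict the result; use of week-2 data would narrow the range.

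Two further inferences are not supported. That the 15% attrition is partly produced by these rules cannot be shown, since the article takes the figure from a cited source. That users of outside treatment must be counted as not effective in the primary analysis does not follow either: the stated primary outcomes are HECSI and NRS scores, and such a rule is a choice of estimand.

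**What to change.** In Textbox 1, separate stopping study treatment from leaving the trial:

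1. Record unexcused missed visits, under 80% of assessments and outside medication as protocol deviations that affect the per-protocol set.
2. Still collect HECSI and NRS at the scheduled week-4 visit from every randomised patient, unless consent is withdrawn, contact is lost or the patient dies.
3. In Data Analyses, impute only values that remain missing.
4. Add a sensitivity analysis that departs from missing at random, for example by assigning unfavourable values to patients who left or used outside eczema treatment.

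When study drug is stopped stays with the investigators.

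The cost is an amendment to the wording and some effort to bring back patients who deviated. Week 4 is already scheduled, so no visit is added and the sample size does not change. The article reports 40 patients recruited by 1 July 2025, so at that date 122 − 40 = 82 were still to be enrolled and could be followed under the revised rule.

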### Concomitant Treatments and Forbidden Drugs

All systemic and topical medications administered to participants during the clinical trial, excluding routine study drugs, will be documented. The reporting period commences from the date of informed consent signing or the randomization date and extends to the final follow-up visit (the date, month, and year of signing will be specified when the informed consent form is signed). Participants must submit their medical history and medication records from the past 3 months to verify medication usage and the date of discontinuation. To eliminate the potential interference from other therapeutic agents, participants are restricted from using systemic corticosteroids, immunosuppressants, biologics, small molecules, or any additional treatments, aside from the standard study medication, from 30 days prior to the informed consent signing or randomization until the final follow-up. Applying topical Chinese patent medicines, corticosteroids, retinoids, calcineurin inhibitors, or other medications is prohibited within 1 week before the final follow-up.

### Recruitment

This research mainly focuses on outpatient individuals from Guang’anmen Hospital, which is connected to the China Academy of Chinese Medical Sciences. This trial is scheduled to conduct a pilot recruitment from March to April 2025 to achieve 5% of the target enrollment. Full patient recruitment is anticipated from May 2025 to March 2026, using advertisements, posters, and physician referrals. The advertisements and posters will provide a brief overview of the trial, outline the inclusion criteria and compensation details, and include the contact information for the researchers. Prior to enrollment, all participants will receive a thorough explanation of the trial procedures, the objectives of the research, possible adverse effects, and expected benefits. During the screening phase, each individual’s eligibility for participation will be evaluated, and they will be informed of their right to withdraw from the study. Those who decide to participate in the trial will be required to complete 2 informed consent documents: one for their records and one to be kept by the research team.

To enhance patient retention, the following measures will be implemented:

Follow-up reminders: SMS text messaging and WeChat (Tencent) reminders will be dispatched 48 hours and 24 hours prior to the appointment.Incentive system: A participant subsidy of 200 RMB (approximately US $27.64) will be provided upon the completion of all follow-up visits.Convenience optimization: Weekend follow-up slots will be made available.

### Randomization, Concealment, and Blinding

This study will use the SAS (SAS Institute) PROC PLAN process statement to generate random numbers to determine the seed number and fragment length. The treatment tasks corresponding to run numbers 001‐120 will be documented. To ensure allocation concealment, the randomization process will be overseen by an independent statistician who is not involved in the study [28]. Eligible participants will be randomly assigned to either the treatment or control groups in a 1:1 ratio. The random numbers will be placed in a closed, opaque envelope, secured in our center. To ensure objectivity, operators will not be aware of any evaluations by efficacy evaluators and vice versa. Only the operators will have access to the random numbers prior to the commencement of the treatment. Further, they are not going to take part in the evaluation. To maintain strict allocation concealment, the system shall log metadata, such as time of randomization, operator’s identity, and IP address. The quality control will regularly check these logs for any violations or deviations. In order to blind the participants, both groups will receive the same package of drug and placebo, with a similar treatment protocol. The placebo will add artificial coloring to ensure size, color, shape, taste, odor, and packaging are all identical to the active drug. Unblinding will occur only after the completion of case collection. However, an emergency unblinding procedure may be initiated if a serious adverse event or urgent medical treatment is necessary during the study.

Furthermore, the quality control team will conduct anonymous surveys at 3 critical stages, including when the trial reaches (1) 50% completion, (2) just before its conclusion, and (3) before unblinding. These surveys will evaluate whether participants, clinical researchers, and efficacy evaluators are aware of the group allocations. The data collected from these surveys will be subjected to statistical analysis to mitigate the risks of performance and detection biases, thereby enhancing the study’s credibility.

### Intervention

Patients will initially dilute the granules (either the moisturizing and anti-itch wash or the placebo wash) in 1500‐2000 mL of hot water during the treatment period. When the medication cools to around 37°C, instruct the patient to fully immerse both hands in the solution for 15 minutes. After this, the medication will be rinsed off. Following the wash, an external cream (either mometasone furoate cream or placebo cream) will be applied to the affected area using the fingertip unit method, where 1 fingertip unit is sufficient to cover the entire hand of an adult (both front and back). The cream will be applied evenly in a thin layer to cover the lesions fully, followed by gentle circular massaging to enhance absorption. This application will occur once daily. Daily care will be administered throughout the day using Xiehe Vitamin E Cream (Product Standard number SuG Cosmetics Network Backup 2019002615). Clinical researchers will distribute medications biweekly to mitigate the risk of early dropout associated with a single 4-week supply. During the week 4 follow-up, both used and unused wash and cream will be collected, and panoramic photographs of the medication bags and tubes (including the participant ID label) will be taken and archived. A follow-up phone check will be conducted for medications that are not returned within 48 hours to confirm usage frequency and document the reasons for nonreturn. The sensitivity analysis will include participants with adherence rates below 80% or exceeding 120%. Furthermore, all medications used in the study will only be distributed after passing quality control testing.

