**Methods:**

This study is a clinical trial characterized as randomized, double-blind, double-dummy, and positive drug-controlled. A total of 122 patients diagnosed with CHE have been randomized and allocated in a 1:1 ratio into 2 distinct groups, with one receiving the intervention and the other serving as the control. Participants in the intervention group will receive RZZYL granules along with a placebo cream of mometasone furoate, whereas the control group will get mometasone furoate cream in combination with a placebo for RZZYL granule. Both groups will be treated with either the active drug or a placebo for 4 weeks. The primary outcome metrics are the Hand Eczema Severity Index (HECSI) and the Numerical Rating Scales (NRS). Secondary outcome metrics consist of the target lesion area score, the Patient-Oriented Eczema Measure (POEM), the Dermatology Life Quality Index (DLQI), and the Investigator Global Assessment (IGA). The outcomes will be assessed at the start of the study and again at 2 and 4 weeks after the treatment period.

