## Methods

### Trial Design

The trial is randomized, double-blind, double-dummy, and positive drug-controlled. The research will be carried out at Guang’anmen Hospital of the China Academy of Chinese Medical Sciences. Before therapy, patients with CHE have standardized baseline examinations, including medical history, physical examination, specialist assessments, and laboratory tests. Dermatologists will conduct the evaluation scales. The hospital’s laboratory and electrocardiogram departments will test blood, urine, and electrocardiogram. All enrolled patients will be randomly assigned to 2 groups: RZZYL (granules) plus mometasone furoate cream placebo and RZZYL (granules) placebo plus mometasone furoate cream. The treatment method for each patient will be the same within their respective groups. The trial will comply with the World Medical Association Declaration of Helsinki and China’s legislation and recommendations on Good Clinical Practice. Informed consent will be acquired from all participants after a comprehensive explanation by the doctors prior to the intervention. The study design is illustrated in Figure 1.

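### The protocol's two adherence rules do not match: an 80–120% range in one section, an 80% floor glossed as 22 days of unspecified medication in the other

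*Protocol article*

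**What the plan says.** Adherence appears in two places in the protocol article.

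- **Intervention.** "The sensitivity analysis will include participants with adherence rates below 80% or exceeding 120" per cent. The scale (days, bags or amount), the product and the analysis are not stated. On accountability, at week 4 "both used and unused wash and cream will be collected, and panoramic photographs of the medication bags and tubes" are taken and archived, with a phone check on usage for medication not returned.
- **Data Analyses, Per Protocol Set.** Participants qualify if "they must have completed at least 80% of the treatment regimen (ie, a minimum of 22 days of medication within 4 weeks"), and if they "have not used prohibited study drugs, and possess complete data for the primary end point (HECSI score"). No upper limit is given, and no count per product.

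The regimen behind these rules is as follows. "Both groups will be treated with either the active drug or a placebo for 4 weeks" (Abstract, Methods). Each patient soaks the hands in the wash, rinses, and then applies the cream; "This application will occur once daily" (Intervention). The arms are "RZZYL (granules) plus mometasone furoate cream placebo and RZZYL (granules) placebo plus mometasone furoate cream" (Trial Design). The active product is therefore the wash in one arm and the cream in the other. The Sample Size section classes the trial as noninferiority.

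**The concern.** The article prints two numerical rules for the same quantity, and they differ in three ways.

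1. One has a ceiling and the other has none.
2. The rule without a ceiling is expressed in days, a scale on which the other rule's ceiling has no meaning.
3. The day figure does not equal the percentage that it is meant to explain.

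The double-dummy design adds a fourth difficulty. The same lapse has different consequences by arm: a missed wash is a missed active dose on RZZYL and a missed placebo on mometasone, and a missed cream is the reverse. One undivided count of medication days cannot separate the two.

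What is at stake is the meaning of the Per Protocol Set. In a noninferiority trial that analysis carries real weight beside the full analysis set, because it should compare patients who took the active treatment they were assigned. Here membership turns on an unstated choice of what counts as a day of medication, and that choice affects the two arms differently.

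**Working it through.** **Inputs.** Treatment lasts 4 weeks, taken as 28 days (Abstract). Use is once daily; the article says so after the cream step, and since the cream follows the wash, the wash is assumed to be once daily too. The limits are 80% and 120% (Intervention), and 80% or 22 days (Data Analyses).

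**Step 1: reproduce the 22-day figure.** 0.80 × 28 = 22.4 days, so the smallest whole number of days reaching 80% is 23 (23/28 = 82.1%). The stated 22 days is 22/28 = 78.6%. It arises only by rounding 22.4 down. It would satisfy 80% only if the treatment period were at most 22/0.80 = 27.5 days. A patient with exactly 22 days therefore meets the Per Protocol day rule and, counted in days, falls below 80% under the Intervention section.

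**Step 2: test the 120% limit on the day scale.** 1.20 × 28 = 33.6. A count of days within 4 weeks stops at 28, which is 28/28 = 100%. More than one use in a day does not add a day. The 120% limit can therefore apply only to amount or number of uses, which is not the scale in Data Analyses. With no ceiling among the Per Protocol criteria, an overuser who meets the others is in the set.

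**Step 3: apply the possible readings of the day count.** Take a patient with cream on 28 days and wash on 18.

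| Reading of the floor | Count for this patient | In the Per Protocol Set? |
|---|---|---|
| Any product makes a day of medication | 28/28 = 100% | Yes |
| Uses pooled over both products (2 × 28 = 56; 80% = 44.8) | 28 + 18 = 46; 46/56 = 82.1% | Yes |
| Both products needed on the day | 18/28 = 64.3% | No |

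On the first two readings, active exposure is 18/28 = 64.3% if the patient is on RZZYL and 28/28 = 100% if on mometasone. The extremes are wider. Under the any-product reading, 22 cream days and no washes would pass. Under pooling, full cream use needs 45 − 28 = 17 washes (17/28 = 60.7%).

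**Step 4: what the sensitivity analysis would vary.** The full analysis set holds all randomized participants, so patients below 80% and above 120% are already in it. Those above 120% can also already be in the Per Protocol Set. Adding patients below 80% to the Per Protocol Set moves it back towards the full analysis set. Read literally, including out-of-range patients tests little that the two main sets do not already show.

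**Direction.** If the wash is the product more often missed, RZZYL patients lose active exposure and mometasone patients do not. Cream overuse raises active exposure only on mometasone. Both would work against RZZYL. If the cream were the product more often missed, the loss would fall on mometasone instead. The documents contain no adherence data and no response rate for patients without the active wash, so the size of any bias cannot be computed.

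**The case against.** The strongest reply is that the regimen is one sequence of soak, rinse and cream. On the ordinary meaning of completing 80% of it, a day with cream alone is not a completed day, and the patient in Step 3 fails. This is a fair reading. A reader might infer that patients who skip the active wash will certainly enter the Per Protocol Set; the text does not support that. It leaves the route open because the explanatory gloss speaks only of days of medication, without naming the product.

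Second, the rules share a nominal 80% floor and serve different purposes: one defines an analysis set and the other names patients for a sensitivity analysis. A patient above 120% can be in the first and still be examined in the second, and a Per Protocol Set without a ceiling is a permissible choice. To call the rules incompatible would therefore go too far. They do disagree on scale, on the ceiling, and at 22 days.

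Third, to include patients in a sensitivity analysis may only mean that it addresses them. That is possible, but the sentence then does not say what is varied.

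Fourth, a journal article condenses, and the adherence formula and weighing of tubes may be in a fuller document. Their absence is not counted here. The mismatch lies between figures that the article itself prints.

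Finally, the likely direction makes a false noninferiority claim less likely, not more. That stands. The risk is mainly a wrong or uninterpretable failure.

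**Conclusion.** The point holds as a mismatch to reconcile. Three parts rest on the text and simple arithmetic, given 28 days of once-daily use: the ceiling exists in one rule only; it cannot operate on a day count (33.6 against a maximum of 28); and 22 days is 78.6%, one day short of the stated 80%. Overusers therefore stay in the Per Protocol Set as written.

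The two-product part is an ambiguity. On an any-product or pooled reading, a patient with 64% active exposure on RZZYL is admitted on the same terms as one with 100% on mometasone; on a both-products reading that patient is excluded. The wash is the more laborious step, so a reader might infer that missed doses will fall mainly on it. That is plausible, but no data in the documents show it. The likely direction, against RZZYL, rests on that assumption, and no magnitude can be attached.

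**What to change.** Reconcile the Intervention and Data Analyses sections into one adherence definition.

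- **Per product.** Compute adherence separately for wash and cream, using the returned bags and tubes already collected. A tube shows amount, not days, so name the administration record that supplies the cream day count.
- **Per Protocol Set.** Require the 80% floor for each product, stated as 23 of 28 days, applied identically in both arms and under blinding.
- **Sensitivity analysis.** Reword it to exclude participants below 80% or above 120%, name the set that it starts from, and define the 120% limit on amount used, with its denominator stated.

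A ceiling for the Per Protocol Set itself and weighing of tubes against a patient-specific expected amount are open to debate and are not needed to resolve the point.

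The cost is a slightly smaller Per Protocol Set and a little more accountability work, with no extra visits or patients. It is best done soon: the Results section reports 40 patients recruited by July 1, 2025, and the rule should be settled before unblinding.
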